### Inclusions/exclusion criteria

The trial will recruit from two defined patient cohorts: (1) newly diagnosed CD patients (or within 3 months of diagnosis) and (2) those with previously confirmed CD with a high clinical suspicion of luminal relapse, requiring radiological investigation.

In the new diagnosis cohort, eligible patients are aged 16 years or older, have given written informed consent, undergoing or having undergone colonoscopy, and either:

•Newly diagnosed (within 3 months) with CD based on endoscopic, histological, clinical and radiological findings, [11] or

•Highly suspected of CD based on characteristic endoscopic, imaging and/or histological features but pending final diagnosis.

In the suspected relapse cohort, eligible patients are aged 16 years or older, able to give written informed consent, with a known diagnosis of CD together with a high clinical suspicion of luminal relapse defined as:

•Objective markers of inflammatory activity (raised CRP >8 mg/L OR raised calprotectin > 100 mcg/g), or

•Symptoms suggestive of luminal stenosis (including obstructive symptoms such as colicky abdominal pain, vomiting) or abnormal endoscopy suggesting relapse.

Patients with any psychiatric or other disorder likely to affect on informed consent and those with evidence of severe or uncontrolled systemic disease, which at the principal investigator’s discretion renders the patient unsuitable for participation in the study, will be excluded. Pregnant patients or those with contraindications to MRE (e.g. allergy to all suitable contrast agents, cardiac pacemaker, severe claustrophobia, or an inability to lie flat) are also excluded. Recruited patients with suspected disease whose final diagnosis is not CD, and those who undergo surgical resection prior to colonoscopy will also be excluded.

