### Sample size

Power is based on the primary outcome stipulated by the HTA: diagnostic accuracy for CD extent. There are two aspects to correctly assigning disease extent; correctly detecting the presence of disease and correctly assigning its segmental location. For example a test which correctly identifies disease in the terminal ileum of the small bowel, but misses disease in the proximal bowel (e.g. jejunum) will conceivably result in an incorrect patient management decision i.e. such a test would be inaccurate for defining the extent of CD. Power is thus based on a two facetted compound accuracy measure (disease presence and disease location) [4,16,17].

A total cohort of 301 (210 patients with disease) is required to detect a 10% superiority of MRE over USS in correctly assigning disease presence and location at 90% power (type 2 error) [18]. Allowing 10% loss to follow up (referring to patients who fail to undergo the complete set of initial imaging – colonoscopy, ultrasound and MRI for new diagnosis patients and ultrasound and MRI for relapse patients – currently this lies at 12%), the total cohort is of 334 patients (167 new diagnosis patients and 167 relapse patients).

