### Analysis

A detailed statistical analysis plan will be produced and finalised prior to data lock and transfer to trial statistician. Analysis will be based on all patients in the study. The primary and secondary outcomes will be based on available case analysis with a sensitivity analysis using multiple imputations, best case and worst case analysis.

Analysis for the primary outcome will use logistic regression of paired binary outcomes for comparison of diagnostic accuracy measures of MRE and USS within patients, allowing adjustment for clustering by centre. 95% confidence intervals will be calculated and p-values of <0.05 will be considered statistically significant. A similar approach will be used for the secondary outcomes.

There will be no adjustment of p-values for secondary outcomes for multiple testing. STATA statistical software will be used.

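### The target of 334 is built on 10% loss while the same sentence reports 12%, and the allowance does not cover recruits later found not to have CD: a minor inconsistency

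*Protocol article*

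**What the plan says.** The Sample size section of the protocol article sets the requirement: "A total cohort of 301 (210 patients with disease) is required to detect a 10% superiority of MRE over USS", with the power given as "at 90% power (type 2 error". It then inflates for attrition: "Allowing 10% loss to follow up (referring to patients who fail to undergo the complete set of initial imaging". The bracket goes on to list the set as colonoscopy, ultrasound and MRI for new-diagnosis patients, and ultrasound and MRI for relapse patients. It ends, with the target, as "currently this lies at 12%), the total cohort is of 334 patients", split as "167 new diagnosis patients and 167 relapse patients".

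A further way out appears under Inclusions/exclusion criteria: "Recruited patients with suspected disease whose final diagnosis is not CD, and those who undergo surgical resection prior to colonoscopy will also be excluded". The same section admits to the new-diagnosis cohort patients in whom CD is strongly suspected but not yet confirmed. No rate, allowance or replacement rule is given for these exclusions.

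On the significance level, the Analysis section says "95% confidence intervals will be calculated and p-values of <0.05 will be considered statistically significant". Sidedness is not stated.

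**The concern.** Two things do not fit together. First, the planned loss and the reported loss describe the same quantity in one sentence and differ, yet the target follows the lower one. Second, the loss is defined narrowly, by completion of initial imaging, while another section removes recruits for a different reason. A patient can have every scan and still leave because the final diagnosis is not CD.

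The primary outcome is a difference in sensitivity, so its power rests on the patients with disease. The total of 301 also supports the specificity comparison, the first secondary outcome. If 334 recruits do not yield 301 and 210, the stated power does not follow from the stated target.

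**Working it through.** **Inputs from the article.** Required: 301 evaluable, 210 with disease, so the diseased share is 210/301 = 0.698. Difference: 10%, read as 10 percentage points, paired within patient. Power: 90%. Loss: 10% allowed, 12% reported. Target: 334.

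**Inputs assumed.** Two-sided 0.05 test, because sidedness is not stated. A discordance proportion ψ (patients in whom exactly one test is correct), because the article gives none.

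**Step 1: reproduce the target.** N = 301/(1 − 0.10) = 334.4, and 334 × 0.90 = 300.6. The stated 334 is reproduced at 10% loss.

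**Step 2: apply the reported 12%.**
- Evaluable: 334 × 0.88 = 293.9, about 294 (7 fewer than 301).
- With disease: 293.9 × 0.698 = 205.1, about 205 (5 fewer than 210).
- Recruits needed to keep 301: 301/0.88 = 342.05, so 343 (9 more than 334).

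**Step 3: power.** For a McNemar comparison with difference d = 0.10 (normal approximation):

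n = [1.96·√ψ + 1.2816·√(ψ − d²)]² / d²

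Setting n = 210 gives ψ = 0.204 (ψ = 0.20 gives 206). Holding ψ fixed:

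Power = Φ{[d·√n − 1.96·√ψ] / √(ψ − d²)}

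- n = 210: (1.449 − 0.885)/0.440 = 1.28, power 90.0%.
- n = 205.1: (1.432 − 0.885)/0.440 = 1.24, power 89.3%.

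A one-sided 0.05 test back-solves to ψ = 0.250 and gives 89.4% at 205, so sidedness hardly matters. The loss of power is about 0.7 points.

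**Step 4: the not-CD exclusion.** No rate is given, so this step is an assumption throughout. Take 2% to 10% of the imaged new-diagnosis half, on top of 12% imaging loss. The evaluable number is then 291 to 279. Two bounds follow for power:
- If none of the excluded would have counted among the diseased, 205 remain and power stays at 89.3%.
- If they are removed at the overall diseased share, 203 to 195 remain and power is 89.0% to 87.7%. This is an upper bound on the harm, because a recruit without CD cannot have small bowel CD.

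**Step 5: how firm is the 12%?** The article gives no denominator. Trial status reports 46 recruits. If the 12% rests on those 46 (an assumption), it is 5/46 = 10.9% or 6/46 = 13.0%. The exact 95% intervals are 3.6% to 23.6% and 4.9% to 26.3%, and both contain 10%.

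**The case against.** The case for leaving the text alone is a fair one. The arithmetic is correct: 10% is the planning value and 12% an early status report. With 46 recruits against a target of 334, an observed 12% does not refute 10%. Taken at face value, it costs 0.7 points of power, 5 diseased patients or 9 recruits. The 12% may even overstate loss from the primary analysis, because a new-diagnosis patient without colonoscopy counts as lost but could still have both index tests and a panel reference. The full protocol, which is not shown, may say whether excluded patients are replaced.

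Most of this stands, and it is why the point is minor. It does not remove the mismatch: the article prints the higher figure, keeps the lower one and gives no reason. It also fixes its own definition of the allowance, and that definition leaves out the not-CD exclusion.

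A reader might infer more, in three ways that the document does not support:
- **That the trial is materially underpowered, with total loss of 15% to 25%.** No passage gives such rates.
- **That patients without a six-month panel reference are a further loss.** Nothing shows that any will lack one. The panel works from whatever data are available up to six months.
- **That resection before colonoscopy is wholly outside the allowance.** For new-diagnosis patients it overlaps, because a missing colonoscopy already counts as incomplete imaging.

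**Conclusion.** The point holds as a minor inconsistency. The target of 334 matches 10% loss and not the 12% reported beside it. If 12% continues, the expected yield is about 294 evaluable and 205 with disease against the required 301 and 210, with power about 89% instead of 90%. The yield figures rest only on the article's numbers and an unchanged diseased share of 69.8%. The power figure also needs the two-sided 0.05 paired test and the back-solved discordance of 20.4%.

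Separately, the allowance omits recruits whose final diagnosis turns out not to be CD. The document cannot size that loss. It would fall mainly on the 301, and so on specificity more than on the primary comparison. It would be wrong to conclude that the primary comparison is seriously short of power.

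**What to change.** In the Sample size section, do one of two things:
- State what 334 recruits are expected to yield at the observed 12%: about 294 evaluable, 205 with disease and power about 89%, with the discordance and sidedness assumed.
- Keep 10% and say why, for example by giving the numerator and denominator behind the 12% and the reason for expecting it to fall.

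In either case, redefine the allowance to include the post-recruitment exclusions listed under Inclusions/exclusion criteria, counting resection before colonoscopy once only. Show any total attrition above 12% as a labelled assumption.

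The cost is a few lines of wording. The downside is that the stated figures become slightly less favourable.

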### Analysis

A detailed statistical analysis plan will be produced and finalised prior to data lock and transfer to trial statistician. Analysis will be based on all patients in the study. The primary and secondary outcomes will be based on available case analysis with a sensitivity analysis using multiple imputations, best case and worst case analysis.

Analysis for the primary outcome will use logistic regression of paired binary outcomes for comparison of diagnostic accuracy measures of MRE and USS within patients, allowing adjustment for clustering by centre. 95% confidence intervals will be calculated and p-values of <0.05 will be considered statistically significant. A similar approach will be used for the secondary outcomes.

There will be no adjustment of p-values for secondary outcomes for multiple testing. STATA statistical software will be used.

## Discussion

### Blinding of trial imaging

Ascertaining the true standalone diagnostic accuracy of an individual imaging test is only possible in the absence of external influences to radiological decision making. Interpretation of MRE or USS is likely to be influenced by knowledge of clinical parameters and findings of other imaging tests. The study methodology has therefore been specifically designed to ensure strict blinding of the radiologists. Radiologists’ information is restricted to the patient cohort (new diagnosis or relapse), and the history of previous surgery; this information would be available in usual clinical care and withholding it would not reflect routine clinical practice. Each recruitment site has identified two participating radiologists so the MRE and USS for each recruited patient can be conducted and interpreted by an independent radiologist. Trial MREs will be reviewed on workstations separate from the hospital reporting platforms, to ensure blinding from other imaging or reports. Similarly, during USS, where interpretation is more “real time”, the radiologist performing USS will be isolated from all material usually available in the clinical setting. The patient and the radiologist will be advised not to converse with the patient regarding current diagnosis during the USS and where feasible the patient will accompanied by the research nurse during the USS.

For those patients who underwent an MRE prior to recruitment, their images will be re-evaluated by an alternate radiologist, blinded to other patient information. For patients who underwent an USS prior to recruitment, their USS will be repeated by an alternate radiologist (unless appropriate blinding of the radiologist performing the original USS can be assured).

### Consensus panel as reference standard and assessment of incorporation bias

There is no single test proven to be a reference standard in the diagnosis of disease presence, extent and activity in CD within the small bowel. In such cases, a consensus panel may be convened to judge the presence or absence of the target condition based on multiple sources of information, as recommended by the HTA [15].

There is significant variation in the construct and behaviour of consensus panels. A recent systematic review of published methods and reporting of studies using expert panels to define the reference standard in diagnostic studies provides recommended options for consensus panels composition, decision making and reporting [19]. One such crucial point is whether or not to incorporate the index tests, MRE and USS, in the consensus review. Inclusion of the index test result may overestimate its importance, leading to incorporation bias, and falsely high accuracy. Conversely, excluding the index test may hamper the ability to make the correct diagnosis, resulting in misclassification of the disease status. Several staged approaches have been proposed, such as those in which the panel forms an opinion without the index tests and these are then revealed for review and a final decision is reached. Such approaches are time and personnel intensive and deemed impractical on such a large scale. In order to minimise incorporation bias, the expertise of all panel members will be recorded as well as the level of consensus reached (majority or unanimous) for the primary outcome. The panel may request review by a second independent panel if they are unable to reach consensus on the primary outcome reference standard (presence and location of small bowel CD).

When defining the reference standard for the primary outcome, the panel will record their confidence in the findings of each contributing test (e.g. all available imaging tests, endoscopy etc.). Specifically they will state if the normality or otherwise of each available test is clear cut or equivocal. Such data will help detect potential incorporation bias (e.g. if an equivocal MRI “overrides” a clear cut CT enterography and USS). The trial statistician and CI will review the outcome of the panel review for the first 50 recruited patients centrally. If incorporation bias is deemed problematic, a decision will be made as to the need for a routine second panel review of cases when the findings of tests contributing to the primary outcome reference are discrepant.

To standardise the decisions of the consensus panel a member of the central trial team will attend each consensus meeting to ensure similar criteria are used in defining disease extent.

The METRIC trial is a multi-centre prospective cohort study comparing the diagnostic accuracy of MRE and USS for the presence, extent and activity of small bowel Crohn’s disease. The lack of a single reference test has led to the use of a consensus panel to act as the reference standard, with specific attention to minimize incorporation bias. The trial methodology includes detailed protocols in order to ensure adequate blinding of radiologists. In addition the trial includes direct recording of patient management decisions resulting from MRE and USS test results, to reduce uncertainty in evaluating the comparative impact of modalities. The sample size of our study is ten times larger than the only other study directly comparing MRE and USS in similar patients (8).

### Trial status

The trial was launched at the main site University College Hospital (London) (UCH) on the fourth of December 2013 and is currently recruiting at five centres – UCH, Leeds Teaching Hospitals, Ninewells Hospital (Dundee), Northwick Park and St Mark’s Hospitals, Oxford University Hospitals, Queen Alexandra Hospital (Portsmouth). Other sites are currently undergoing site-specific initiations. The trial has recruited 46 patients – 14 in the New diagnosis arm and 32 in the relapse arm.

## Abbreviations

BaF: Barium follow through; CD: Crohn’s disease; CRF: Case report form; CRP: C Reactive protein; CT: Computed tomography; FC: Faecal calprotectin; GCP: Good clinical practice; HAI: Histological activity index; HBI: Harvey bradshaw index; MRE: Magnetic resonance enterography; NHS: National health service; REC: Research ethics committee; T: Tesla; UCH: University College Hospital (London); USS: Ultrasound scan.
